### Participants

A total of 140 patients and/or relatives will be selected from the home care and inpatient unit of CUDECA foundation where the ITV-Pal programme will be implemented. This sample size is enough to detect a mean difference of 3 in the HAD scores between groups of 25%, with a power of 80% and a confidence level of 95%.^24^ Sample size was adjusted according to the standard criteria for cluster randomised trials, using the design effect (DE) of 1.3. The DE was calculated as follows: DE=1+(nc–1)×ICC (where nc is the mean number of individuals in the cluster and ICC the intracluster correlation coefficient). The ICC in the present work was considered to be 0.05 and the mean cluster size was assumed to be 7. A potential loss of 20% was estimated. Therefore, 140 patients/relatives and 20 volunteers are required.

The inclusion criteria will be: patients and relatives cared for by a specialised PC team; to be over 18 years of age; consenting to participate in the study by signing the informed consent form. Subjects who have specific conditions reducing their physical ability to use the devices, for example, visual, hearing or motor impairments will be excluded from the study.

The HCP involved in these services will be included to measure the success of implementing the programme.

The inclusion criteria for volunteers will be an interview with the Volunteer Department and having completed basic care training to be able to carry out their work. Also, a commitment to participate in the study for 1 year. For this reason, more volunteers will be trained as needed during the 2 years of implementation.

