#### Patients

The ICECAP Supportive Care Measure (ICECAP-SCM) 25 has been developed as a tool for use in economic evaluation conducted in an end of life setting for patients. The questionnaire covers the attributes of: choice, love and affection, physical suffering, emotional suffering, dignity, being supported and preparation with the lowest score being 1 and the highest score being 4.EuroQol-5D-5L,^26^ a generic, brief and easy-to-use questionnaire designed to describe and assess the current health-related quality of life of the person completing the questionnaire. Primary outcome: The descriptive system comprises five dimensions: mobility, self-care, usual activities, pain/discomfort and anxiety/depression. Each dimension has five levels: no problems, slight problems, moderate problems, severe problems and extreme problems. The patient is asked to indicate his/her health state by ticking the box next to the most appropriate statement in each of the five dimensions.Distress thermometer^27^ was developed as a simple tool to effectively screen for symptoms of distress. The instrument is a self-reported tool using a 0–10 rating scale.Edmonton Symptom Assessment Questionnaire^28^ used to rate the intensity of nine common symptoms experienced by cancer patients, including pain, tiredness, nausea, depression, anxiety, drowsiness, appetite, well-being and shortness of breath where 0 is that the symptomatology does not affect him/her at the moment and 10 with the highest intensity.Tech-PH^29^
an instrument for measuring older people’s attitudes toward technology: It was created from the six items in the two factors, techEnthusiasm and techAnxiety. TechPH could be interpreted on a five-point response scale, ranging from 1 (fully disagree) to 5 (fully agree), where the higher the index indicates a higher level of technophilia.The Questionnaire on the Frequency of and Satisfaction with Social Support (QFSSS)^30^ was designed to assess the frequency and degree of satisfaction with perceived social support from different sources in relation to three types of support: emotional, informational and instrumental. Both frequency and satisfaction are measured on a Likert scale of 1–5.Hospital Anxiety and Depression Scale (HADS)^31^ instrument to measure anxiety and depression in a general medical population of patients. The lowest score being 0 and the highest score being 3.

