### Data collection and follow-up

The recruitment of the volunteers began in March 2021. When they finished their training, the new service started in September 2021 which was when patients/relatives recruitment started. Volunteer recruitment will be active during the whole study every 3 months. Recruitment is expected to end in September 2023.

The care teams offer the accompaniment of a volunteer to the patient/relatives. If they accept the accompaniment and participate in the study (if they want the accompaniment of a volunteer but do not want to participate in the study, the volunteer will be offered anyway). Once the informed consent to participate in the study has been signed, the data collection will proceed as described below. Further details can be seen in figure 1.

Patients/relatives who consent to participate (intervention and control group) will be invited to fill in at least three short questionnaires: at the time of recruitment for this study, 15 days after recruitment following the volunteer service experience (if hospitalised), and every month as long as the patient remains under PC care or until death. During the follow-up, patients and relatives will be asked if there is any change in their condition with respect to the questions asked at baseline. In this way, costly follow-up will be avoided. A maximum of 5 patients/relatives will also be invited to participate in an in-depth interview at various points during the implementation of the programme.

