### Data analysis

#### Quantitative data

Intention-to-treat principle: Descriptive statistics will be used to summarise subject characteristics (age, gender, education, religion, socioeconomic status, marital status, place of residence) and the process evaluation. Basal comparison between groups for independent samples: Student’s t-test or χ^2^ test; for related samples: analysis of variance for repeated measures to analyse changes within groups. Multilevel analysis will be used for main and secondary outcomes. A multilevel modelling approach will be used to examine the difference in the primary endpoint between patients/relatives, taking account of clustering effects at volunteers level. All statistical tests will be two sided and considered significant if p<0.05. Repeated measurements of analyses of variance will be conducted to assess the development of endpoints over time. Multivariate Imputation will be used to handle missing data.

Also, outcome data will be collected for patients and relatives: the cost-effectiveness of care of dying patients, including the volunteer training programme, will be assessed by calculating the incremental cost-effectiveness ratio (ICER). The ICER is defined as the difference in total healthcare costs in the intervention group (including the costs of performing the intervention) compared with the total costs in the control group, divided by the difference in outcomes.^36^ Outcomes will also be measured as QALYs using the EQ-5D health-related quality of life questionnaire. We will also use the capabilities approach (ICECAP). The potential impact of the programme beyond the trial period will be extrapolated using modelling techniques.

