#### Cost–utility ratio

This is an exploratory objective (for which a specific design has not been applied). The cost–utility ratio will be estimated by dividing the total cost by the sum of the potential gains expressed in QALYs.

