## Discussion

The COVID-19 pandemic is changing the way we are interacting, launching us seemingly overnight from the real world into the virtual world, and seeking ways to address the challenges of social distance.^39^ Face-to-face support of PC volunteers has temporarily been suspended, so creativity and innovative solutions are needed to continue providing this care and support. The use of information and communication technologies and, specifically, NT, allows us to rethink the way volunteers act by integrating these resources to create ‘tech-volunteers’ that will attend to their needs in a different way and also support new needs that have emerged more clearly now due to social distance, with a broader reach.^40^ The United Nations Online Volunteer Programme states: ‘Online volunteering is fast, easy—and most of all, effective when skilled, passionate individuals join forces online with great organisations, everyone wins’ but no robust study has been carried out to support this statement. In this way, this study will bring the real evidence toward NT integration as a useful tool not only to facilitate communication between volunteers and patients/relatives, but also to turn NT into instruments that support daily living and enhance care, when in the hands of trained tech-volunteers.

Although this new volunteer programme will be implemented during the pandemic to analyse the effects on patients and their relatives, we hope that training in NT will make it easier for PC volunteers to offer new skills and increase the satisfaction of the people they accompany.

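### One two-sided p<0.05 rule covers every main and secondary outcome, and the primary is too unsettled (scale, population, time) to work as a hierarchy

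*Protocol article*

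**What the plan says.** Under Data analysis, Quantitative data, the protocol article states "Multilevel analysis will be used for main and secondary outcomes". It then says of one endpoint, which it does not name, "A multilevel modelling approach will be used to examine the difference in the primary endpoint between patients/relatives". The decision rule follows: "All statistical tests will be two sided and considered significant if p<0.05". Repeated-measures analysis of variance is added for development over time.

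Three other sections bear on what the primary is:

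- **Variables, Patients.** The label appears inside the EuroQol-5D-5L entry: "Primary outcome: The descriptive system comprises five dimensions: mobility, self-care, usual activities, pain/discomfort and anxiety/depression".
- **Participants.** The trial is sized on another scale: "This sample size is enough to detect a mean difference of 3 in the HAD scores between groups of 25" (a percent sign follows in the text). The 140 participants are patients and/or relatives, counted together.
- **Data collection and follow-up.** Assessments are at recruitment, at 15 days (if hospitalised), and "every month as long as the patient remains under PC care or until death". No visit or contrast is named as deciding.

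The Variables section lists seven instruments for patients and seven for relatives. The one objective marked as exploratory is cost–utility: "This is an exploratory objective (for which a specific design has not been applied".

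**The concern.** A primary endpoint controls error only if a reader can tell, before the data are seen, which test decides. Here three parts of that definition are open: the scale, the population and the time. The one rule that is fixed treats every test alike. Followed as written, a significant result on HADS or EQ-5D-5L, in patients or in relatives, could each be presented as the primary finding, and any other scale could be called significant at the same level.

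This matters because the trial is described as a test of efficacy under Study design, and the Discussion expects that "this study will bring the real evidence toward NT integration as a useful tool". If a single significant scale out of many can carry that statement, its real error rate is several times the nominal 5%.

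**Working it through.** **1. The plan's own figures.** The design effect is 1 + (7 − 1) × 0.05 = 1.3, as stated. The 140 cannot be reproduced from the stated inputs alone, because no SD is given. With an assumed SD of 5 and a difference of 3, two-sided 5% and 80% power:

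- n per arm = 2 × 5² × (1.960 + 0.842)² / 3² = 43.6, so 44.
- Both arms with the design effect: 88 × 1.3 = 114.4.
- After 20% loss: 114.4 / 0.8 = 143, close to 140.

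An SD of 4 gives 91 and an SD of 6 gives 205. The stated size is therefore consistent with a single HAD comparison at 5%, with patients and relatives pooled. The document gives no family-wise error rate. Its only error figure is 5% per test.

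**2. Counting the tests** (one test per scale).

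- Patients, 7: ICECAP-SCM, EQ-5D-5L, distress thermometer, Edmonton, TechPH, QFSSS, HADS.
- Relatives, 7: ICECAP-CPM, EQ-5D-5L, distress thermometer, TechPH, QFSSS, HADS, iCODE.
- Candidate primary tests: 2 scales (HADS, EQ-5D-5L) × 2 populations = 4.
- All listed scales: 7 + 7 = 14.
- A reduced family without the two ICECAP measures (described as tools for economic evaluation) and the two TechPH scores (tied to describing the technological profile): 14 − 4 = 10.

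Sub-scores, separate visits and the volunteers' scales are not counted.

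**3. Formula.** With no true effect and independent tests, the chance of at least one p<0.05 in either direction is 1 − 0.95^k. The chance of at least one in the benefit direction is 1 − 0.975^k. For k = 4: 1 − 0.95⁴ = 18.5%. For k = 14: 1 − 0.95¹⁴ = 51.2%, and 1 − 0.975¹⁴ = 29.8% for benefit.

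For tests with equal correlation ρ, the test statistics are normal with a shared component, and the two-sided chance is 1 − ∫ [Φ((1.96 − √ρ·x)/√(1−ρ)) − Φ((−1.96 − √ρ·x)/√(1−ρ))]^k φ(x) dx. For benefit only, the second Φ term is dropped. The correlation is an assumption; the documents give none.

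| Tests | Direction | ρ = 0 | ρ = 0.5 | ρ = 0.8 |
|---|---|---|---|---|
| 1 | either | 5% | 5% | 5% |
| 4 | either | 18.5% | 15.6% | 11.4% |
| 7 | either | 30.2% | 23.0% | 14.9% |
| 10 | either | 40.1% | 28.7% | 17.3% |
| 14 | either | 51.2% | 34.8% | 19.7% |
| 1 | benefit | 2.5% | 2.5% | 2.5% |
| 14 | benefit | 29.8% | 17.4% | 9.9% |

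Treating patients and relatives as two blocks of seven with lower correlation between blocks gives 31% to 47% in either direction, depending on the correlations chosen. The expected number of false positives among 14 tests is 14 × 0.05 = 0.70, whatever the correlation.

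**4. Reading the table.** At ρ = 0.5 the 14-test figure is 34.8 / 5 = 7.0 times the single-test rate in either direction, and 17.4 / 2.5 = 7.0 times for benefit. The four-test figure is 11.4 / 5 = 2.3 to 18.5 / 5 = 3.7 times.

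**The case against.** The strongest reply is that a journal article condenses the full protocol, and that multiplicity rules for secondary outcomes are commonly left to an analysis plan, which is not shown. That stands as far as it goes: the absence of an adjustment or testing order is not the finding. The finding is a rule the article does state, applied to every test, together with a primary on which its own sections disagree. An analysis plan that reserved significance for one test would have to override that sentence.

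Several stronger readings are tempting and the document does not support them:

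- **That there is no hierarchy.** Main and secondary outcomes are distinguished and a primary endpoint is mentioned. What is missing is a hierarchy that can be used.
- **That nothing is labelled exploratory, or that all else is therefore confirmatory.** Cost–utility carries the label. That does not make every other outcome confirmatory, and the article also speaks of piloting. The clinical secondaries simply have no stated status.
- **That every visit is tested at 5%.** The plan names multilevel models and repeated-measures analysis, not tests visit by visit. Nor does the text list which instruments recur at follow-up, and the schematic is not shown.
- **That a false benefit is likely, at 35%.** The 35% counts differences in both directions, harm included, and is below one half. For benefit the matching figure is about 17%.
- **That power for the main outcome is poor.** The document states 80%, and nothing here shows otherwise.

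It is also fair to say that 14 is a generous count, since some scales serve the economic evaluation or the technology profile. With 10 scales the either-direction figure is still 17% to 40%.

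**Conclusion.** The point holds in a limited form. The protocol article fixes one significance rule for all outcomes, while its primary is contradictory on scale (EQ-5D-5L label against HAD sizing), unclear on population and silent on time, so the nominal primary/secondary split gives no protection. With no true effect and one test per scale, the chance of at least one significant difference in either direction is about 11% to 19% for the four candidate primary tests, and about 20% to 51% for all 14 scales, instead of 5%. These ranges cover correlations from 0.8 down to 0. The size depends on the assumed correlation and count, but the direction does not: even the narrowest family, limited to the article's own ambiguity, at least doubles the stated rate.

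**What to change.** Reconcile the Participants, Variables and Quantitative data sections so that the efficacy conclusion rests on one between-arm contrast from the multilevel model at two-sided 0.05. Name its score, its population, and either one time point or one defined over-time contrast that is available in both the home care and inpatient settings. The 15-day assessment is tied to hospitalisation, so it may not qualify.

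Replace the blanket p<0.05 sentence. State that all other clinical outcomes, and the results of the other population, are secondary or exploratory and will be reported as estimates with 95% CIs and without an efficacy claim. If a confirmatory claim is wanted for one or two secondaries, name them and test them in a fixed order after the primary, or apply Holm to that short list.

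The cost is a few sentences, with no added participants or data for the multiplicity change itself. The downside is that a secondary result, or a result in the other population, can no longer be called significant on its own. If the reconciled primary is not the HAD score, the sample size justification must be redone for the score chosen.

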#### Qualitative data

Thematic analysis,^36^ with an iterative approach to coding and analysis. For example, what was said by one participant may inform or shed light on the words of another participant. Analysis will focus on the ‘substance of the interview’ to interpret ‘meanings and perceptions’ created and shared during a conversation. Analysis of the data will explore the ideas, assumptions or concepts underpinning what participants are saying. Words or phrases will be coded at latent and semantic level to ‘label’ meaning identified by those words/phrases. ‘Themes’ will then be developed from these codes around a ‘central observation’ or concept to reflect patterns of shared meaning.^37^ For example, to capture ‘something important’ about how these participants make sense of, and use, the ITVPal Programme within the context of end-of-life care.

Analysis will be conducted within a constructionist paradigm, which asserts that meaning and experience are socially produced. Stages of analysis will be iterative and cyclical rather than linear and analysis may move back and forth between stages. In summary, these principles are^36^:

Familiarisation and immersion with the data: repeated reading of the interviews.Generation of initial codes: annotations of initial thoughts against items/categories of text.Creating themes from codes: the minor items/categories that have initially been identified from the text will then be interrogated to generate overall ‘themes’. Engaging with relevant published literature (theoretical perspectives and relevant research) should further enhance the evolving interpretation.Reviewing themes: ensure all collated extracts of text form a coherent pattern, reorganising and refining themes as required.Defining and naming themes: to define the ‘essence’ of what a theme is about.Reporting the analysis: a narrative ‘story’ of the data to provide a concise, coherent, logical account.

#### Cost–utility ratio

This is an exploratory objective (for which a specific design has not been applied). The cost–utility ratio will be estimated by dividing the total cost by the sum of the potential gains expressed in QALYs.

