#### A: Quantitative approach

Pragmatic cluster randomised clinical trial to test efficacy (the unit of randomisation is the volunteer and the unit of analysis is the patient/relatives). A pragmatic cluster randomised controlled trial has shown to be the most appropriate design when the programmes are more focused on the organisational level.^22 23^ For our study, the cluster design is based on two levels: the higher or second level is represented by the volunteer (over volunteer the intervention is conducted, ITVPal Programme: Tech-Volunteer Programme in Palliative Care Services), and the lower or first level being represented by the patients/relatives, who have agreed to participate and are going to receive the tech-volunteer care from volunteers of ITVPal Programme.Before-and-after design for satisfaction of volunteers and HPC with the intervention and its implementation to test effectiveness. The design involves evaluating the effects of a deliberate intervention (introduction of ITVPal Programme) by comparing the outcomes of study participants investigated before the intervention with those measured afterwards.Cost–utility study from the perspective of the funder with a time horizon of 2 years. A detailed cost analysis including costs for the adaptation of a volunteer standard course to an ITVPal Programme as well as the recruitment and training costs of the volunteers will be performed.

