#### Intervention

A complex intervention will be carried out in two phases.

First phase: training of volunteers in NT. Volunteers will be trained in the use of NT and their interconnectivity as tools to support their work as volunteers.The topics that will be covered in the volunteer training are the role of the volunteer, use of NT, communication strategies, complicated situations, self-care, summary and closure of the training. All of this is divided into 10 sessions, each lasting approximately 3 hours. This training will be integrated into the specific training programme for PC care volunteers.The control group, on the other hand, will receive the standard training that the care volunteers have received so far.Second phase: volunteer accompaniment of patients/relatives. During the activities carried out by the volunteer with the patient for accompaniment and leisure. It will have the support of a technological device to be used according to the needs of the patient/relatives (eg, internet searches on a topic of interest, video calls, phone calls, virtual visits) It will be an outcome of the study to know what the device has been used for.The control group will accompany patients without using the NT as usual.

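### The cost–utility section divides total cost by QALY gains without subtracting control-arm cost, which conflicts with the incremental ratio defined under Quantitative data (wrong as written, minor)

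*Protocol article*

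**What the plan says.** The protocol article gives two rules for cost per QALY.

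- **Data analysis, Quantitative data.** "The ICER is defined as the difference in total healthcare costs in the intervention group" (with the cost of delivering the intervention included) "compared with the total costs in the control group, divided by the difference in outcomes". The same paragraph adds: "Outcomes will also be measured as QALYs using the EQ-5D health-related quality of life questionnaire". Together these define an incremental cost per QALY against control.
- **Cost–utility ratio.** The ratio "will be estimated by dividing the total cost by the sum of the potential gains expressed in QALYs". No cost difference is taken and the control group is not mentioned. The section describes its own status as follows: "This is an exploratory objective (for which a specific design has not been applied").

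Two other places matter. The Intervention section makes the comparator an active service: "The control group will accompany patients without using the NT as usual". Section A (Quantitative approach) lists the cost–utility study among the quantitative designs, as a "study from the perspective of the funder with a time horizon of 2 years".

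**The concern.** Both formulas purport to give cost per QALY for the same trial, yet they are different quantities. Control patients also receive volunteer accompaniment, so the economic question is what the technology component adds in cost and in QALYs over that service. A ratio that does not subtract the control arm's cost cannot answer it.

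The section that carries the name of the cost–utility ratio is the one with the non-incremental numerator. An analyst who follows it would report a cost per QALY that a reader could take for an incremental one. This is not a detail left to a fuller document: the article states a formula, and that formula disagrees with another one it states.

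**Working it through.** The article gives no cost, QALY value, ratio or threshold, so there is no figure of the plan's own to reproduce. The check compares the two definitions by algebra and then on assumed inputs.

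**Notation.** C and Q are mean cost and mean QALYs per patient; I is intervention and C is control as a subscript.

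**Quantitative data rule:** ICER = (C_I − C_C)/(Q_I − Q_C).

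**Cost–utility ratio rule:** total cost / sum of QALY gains. Neither term is defined, so three readings were tried:

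- A, intervention arm alone: C_I/Q_I
- B, both arms pooled with equal arm sizes: (C_I + C_C)/(Q_I + Q_C)
- C, gains taken as gains over control: C_I/(Q_I − Q_C)

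**Algebra.** Reading A equals the ICER only if C_I × (Q_I − Q_C) = Q_I × (C_I − C_C). This reduces to C_I/Q_I = C_C/Q_C, meaning both arms have the same average ratio. Reading C equals the ICER plus C_C/(Q_I − Q_C), so the two agree only if control cost is zero.

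**Numbers.** All inputs are assumptions for illustration. Control is fixed at cost 5,000 and 0.10 QALY, an average ratio of 5,000/0.10 = 50,000.

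| C_I | Q_I | ICER | Reading A | Reading B | Reading C |
|---|---|---|---|---|---|
| 5,300 | 0.11 | 30,000 | 48,182 | 49,048 | 530,000 |
| 5,300 | 0.12 | 15,000 | 44,167 | 46,818 | 265,000 |
| 6,000 | 0.12 | 50,000 | 50,000 | 50,000 | 300,000 |
| 4,800 | 0.11 | −20,000 | 43,636 | 46,667 | 480,000 |
| 5,300 | 0.095 | −60,000 | 55,789 | 52,821 | −1,060,000 |

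First row in full:

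- ICER: (5,300 − 5,000)/(0.11 − 0.10) = 300/0.01 = 30,000
- A: 5,300/0.11 = 48,182
- B: 10,300/0.21 = 49,048
- C: 5,300/0.01 = 530,000, which is 30,000 + 5,000/0.01

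**What the rows show.**

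- In the last row the intervention costs more and yields less, so it is dominated. Reading A gives 55,789, which signals nothing.
- In the fourth row the intervention costs less and yields more, so it dominates. Reading C gives 480,000, which looks very expensive.
- Over these sets the ICER runs from −60,000 to 50,000, while Reading A stays between 43,636 and 55,789. Reading A hardly responds to the comparison of interest.
- Agreement occurs only in the special case of the third row, where both arms average 50,000, and Reading C still differs there.

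**The case against.** The best defence is that the incremental comparison is already planned. Quantitative data commits to a ratio against control and names QALYs as an outcome, and the cost–utility objective is declared exploratory. This stands, and it limits the point to one ratio and to minor severity.

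A second defence is that the wording is loose rather than plainly non-incremental. The word gains can mean gains over control. Total cost might mean only the programme's added cost, since section A describes costing the adaptation of the standard course and the recruitment and training of volunteers. The ratio would then be partly incremental, though it would still leave out differences in healthcare cost. That reading is possible but not stated, and the literal words are total cost. Reading gains as gains over control does not help by itself, because the numerator remains total.

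Three stronger readings are tempting, and the documents do not support them:

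- **That the whole economic evaluation fails to compare the arms.** Quantitative data does compare them, and nothing says the cost–utility formula displaces that ratio.
- **That perspective and horizon also conflict.** Section A sets a funder perspective and 2 years, while Quantitative data counts total healthcare costs and says: "The potential impact of the programme beyond the trial period will be extrapolated using modelling techniques". A funder perspective can include healthcare costs, and a modelled extension can sit beside a 2-year analysis. No contradiction is shown.
- **That the article should have specified how QALYs are accumulated or how uncertainty is estimated.** An article commonly leaves such detail to the full protocol or analysis plan.

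**Conclusion.** Wrong as written, minor. The formula under Cost–utility ratio conflicts with the incremental ratio under Quantitative data. Taken literally, it does not measure the added cost per added QALY of the tech-volunteer service over usual volunteering. The fault is confined to that exploratory ratio. It does not touch the primary outcome, the sample size or data collection.

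The size and direction of any error in this trial cannot be computed. A reader might take the illustrative figures as a forecast of bias, but they rest wholly on assumed inputs, and the readings depart from the incremental ratio by very different amounts and not always in the same direction. They show only that the two definitions are not interchangeable. The conclusion that the definitions differ rests on the stated wording and the algebra, not on those inputs.

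**What to change.** Under Cost–utility ratio, replace the formula with the ratio from Quantitative data, using QALYs as the outcome:

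(mean cost, intervention − mean cost, control) / (mean QALYs, intervention − mean QALYs, control)

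Alternatively, delete the formula and refer to Quantitative data. The exploratory label can stay.

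The change costs one sentence. It uses the cost and EQ-5D data already planned and needs no new data collection or change to the design.
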